## Methods: monitoring

The research investigator group meets bi-monthly and oversees decisions on study design and protocol, milestones, ethics and governance, data monitoring, trial conduct, budget and research dissemination. A Benchmarking Co-Design committee and four task groups inform the benchmarking with continuous improvement model build and approach. Adverse events or unintended effects of trial conduct or trial interventions spontaneously raised by partners and/or participants are reported to the research investigator group.

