**Fig. 3 Fig3:**
[figure not shown]
The benchmarking and continuous improvement cycle of assessment, feedback, action planning and implementation. Adapted from the PLAN-DO-COLLECT-LEARN cycle, Menzies School of Health Research [63]. This figure shows the four components of the cycle and the sharing of this information with store directors/owners as represented by the middle section of the figure. Artwork by Ngarrindjeri artist [name]

Control stores receive an in-store assessment of their best-practice implementation at one time each year for three years (2022, 2023, 2024) and provide weekly store sales data (52 weeks pre to 52 weeks post intervention). They are offered a full benchmarking cycle in 2024, prior to which they will continue with usual retail practice.

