*Assessment* of i) POLICY: adoption of health-enabling best-practice store policy, ii) PRACTICE: implementation of best-practice, iii) PRICE: price of a standardised healthy diet, iv) PURCHASING: healthiness of customer purchasing; v) ENVIRONMENT SCAN: Influence of enabling/impeding environment-level factors on healthy in-store operations such as disruptions to food delivery, power outages, and infrastructure.*Feedback*: Within 2-3 months of assessment, intervention stores receive a visual feedback report, with results for their Policy, Practice, Price and Purchasing indicators benchmarked against best-practice targets, all stores, and their progress over time. These reports give data-informed recommendations for performance improvement and feedback on the environmental-level factors.*Action Plan*: Partners present the feedback report to community store directors (store committee/board) in a face-to-face meeting and co-design a feasible and acceptable action plan to improve performance with the ‘who’, ‘how’ and ‘when’ described. Strategies to be employed as part of the action plan may include 'No price promotions on discretionary food and drink products', 'Price discounts on fruit and vegetables', 'No discretionary food and drink products in highly visible/high traffic areas of the store including front-of-store, check-outs, end-of-aisle caps'*Action Implementation*: The co-designed action plan is implemented by the store staff with assistance from the partners prior to the next assessment. Nutrition practitioners are encouraged to maintain regular communication with store staff to maintain motivation. Control stores receive an in-store assessment of their best-practice implementation at one time each year for three years (2022, 2023, 2024) and provide weekly store sales data (52 weeks pre to 52 weeks post intervention). They are offered a full benchmarking cycle in 2024, prior to which they will continue with usual retail practice.

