#### Strategies to improve adherence to intervention protocols

The research team provide training in the benchmarking intervention to nutrition practitioners and coaching as requested. Implementation is monitored using i. a resource-use survey (completed by nutrition practitioners after each benchmarking component, for the purpose of the economic evaluation), ii. documentation of action-plan summaries (using an excel spreadsheet), and, iii. logging of survey completions in REDCap. Interviews are conducted with partner representatives, store directors/owners and managers in 2023 and 2024 (following the Action Plan component of the cycle) to assess implementation and adoptability.

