iv) Purchasing: Healthiness of customer purchasing	Intervention and control stores (2021–2025)	Trained partner nutrition practitioners/research team	Weekly sales data provided by store businesses (Product identifier, Product description, quantity sold, dollar value) [66].	Varies depending on store point of sale systems
v) Environment Scan: Level of influence of environmental-level enabling/impeding factors	Intervention and control stores (2022*, 2023, 2024) *2022 – Intervention only	Store owner/s (for privately owned stores), store representatives, or store nutritionists for stores with ALPA or Outback Stores (with or without store managers and/or area managers)	Environment scan: 26-item e-survey to collect data on the broader socio-ecological impacts on store practice. Survey informed by publicly available submissions to a Parliamentary Inquiry and the Good Food Planning Tool [67, 68]. Co-designed with stakeholders and built in REDCap	~ 15 min

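### Spontaneous-only reporting of unintended effects, with heavier planned contact in intervention stores, cannot support a between-arm statement on effects that sales and price data do not show

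*Protocol article*

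**What the plan says.** The article has one sentence on how harms enter the record, under Methods: monitoring: "Adverse events or unintended effects of trial conduct or trial interventions spontaneously raised by partners and/or participants are reported to the research investigator group". It describes no scheduled or prompted question about harms in either arm.

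Other sections fix how much contact each arm has.

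- **Intervention stores** (Intervention, components of the cycle): "Partners present the feedback report to community store directors (store committee/board) in a face-to-face meeting", and during implementation "Nutrition practitioners are encouraged to maintain regular communication with store staff to maintain motivation".
- **Control stores** (same section): "Control stores receive an in-store assessment of their best-practice implementation at one time each year for three years (2022, 2023, 2024"). On benchmarking itself: "They are offered a full benchmarking cycle in 2024, prior to which they will continue with usual retail practice".
- **Interviews** (Strategies to improve adherence): "Interviews are conducted with partner representatives, store directors/owners and managers in 2023 and 2024 (following the Action Plan component of the cycle"). The arm is not stated, but control stores have no action plan before their 2024 cycle.
- **Environment Scan** (Table 1): "Intervention and control stores (2022*, 2023, 2024) *2022 – Intervention only".

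The Blinding section says that only those analysing the outcomes are blinded.

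**The concern.** A spontaneous report needs someone who notices an event, thinks it worth raising and has an occasion to raise it. In this trial the occasions differ by arm, and the partners, one of the two reporting sources, also deliver the intervention. A larger count in intervention stores may reflect only more conversations. A low count in either arm may reflect only that nobody asked.

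Unintended effects are foreseeable. Action plans may include ending price promotions on discretionary products and moving them out of prominent areas. The Background treats the absence of adverse business impact as a key result of the earlier trial, yet Outcomes lists no business outcome here. The article also says that the strategy should do no harm to communities (Table 2, item 9) and anticipates scale-up across jurisdictions if it is adoptable and effective. Spontaneous reports alone would be a weak basis for a statement on harm at that point.

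**Working it through.** The plan gives no figure on this point, so there is none to reproduce. The check sets out scheduled contacts by arm and then illustrates what unequal contact does to ascertainment.

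**Step 1. Contacts from first feedback (October/November 2022) to the end of 2023.** Effects of feedback or action planning cannot surface earlier.

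- Intervention: 2023 assessment (1), 2023 Environment Scan (1), 2023 interview (1), action-plan meetings (1 or 2). The second meeting follows reports sent in October/November 2023 and may fall in 2024. Total 4 to 5.
- Control: 2023 assessment (1), 2023 Environment Scan (1), interview (0 or 1). The store-manager interview under Relevant concomitant care is not restricted by arm, so controls may have it. Total 2 to 3.

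The 2023 price survey is taken as part of the assessment visit in both arms (assumption). Unscheduled contact is not counted in either arm. The article encourages it during action implementation, which control stores do not have before 2024.

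**Step 2. Illustration.** Suppose every store has one event and each contact brings it to light independently with probability p. With k contacts, the chance that it is heard about is 1 − (1 − p)^k. Neither p nor the one-event premise comes from the document.

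| Assumed p | Intervention, k = 4 | Intervention, k = 5 | Control, k = 2 | Control, k = 3 |
|---|---|---|---|---|
| 0.05 | 18.5% | 22.6% | 9.8% | 14.3% |
| 0.10 | 34.4% | 41.0% | 19.0% | 27.1% |
| 0.20 | 59.0% | 67.2% | 36.0% | 48.8% |

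For example, at p = 0.10: 1 − 0.9^4 = 0.344; 1 − 0.9^5 = 0.410; 1 − 0.9^2 = 0.190; 1 − 0.9^3 = 0.271.

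**Step 3. In stores.** With 15 intervention and 17 control stores and p = 0.10, the expected number heard about is 15 × 0.344 = 5.2 to 15 × 0.410 = 6.1, against 17 × 0.190 = 3.2 to 17 × 0.271 = 4.6. True rates are equal by construction. The ratio of proportions runs from 0.344/0.271 = 1.3 to 0.410/0.190 = 2.2.

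**Step 4. What other data cover.** Weekly quantity and dollar value come from both arms (Table 1), so lost sales and average unit price can be compared. The price survey runs in both arms in 2023. Core-product and sodium purchasing are secondary outcomes. None of these shows complaints, write-offs, staff burden or community reaction.

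**The case against.** The strongest reply is that no between-arm comparison of spontaneous reports is announced. The sentence sits under monitoring and routes concerns to an oversight group, and the full protocol, which is not shown, may hold more detailed procedures. This stands, and it limits the point to what the published rule can support.

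A reader might infer that harms in control stores are simply missed. The documents do not support that. The reporting route is open to all partners and participants, every eligible store is serviced by a partner's nutrition practitioner, and control stores are assessed each year. Under-ascertainment is likely; complete loss is not shown.

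A reader might also infer that no harm can be compared between arms. That is too strong, because sales value, price, core-product and sodium data exist for both.

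The illustration can be attacked as well: p is assumed, and the rule concerns effects of the trial, which are not expected at equal rates in stores without feedback or action planning. Both are fair. The illustration shows direction and plausible order only.

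Finally, the Environment Scan is not a perfect vehicle. For stores with the two retail partners, the store nutritionist may answer it, and the article's 2024 DOI suggests that the 2023 round has passed. The fix has to deal with both.

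**Conclusion.** The point holds in limited form. The article provides only for spontaneous reporting, planned contact before 2024 is heavier in intervention stores, and those who report are unblinded. Reports gathered this way are prone to differential ascertainment and cannot support a between-arm statement on effects that sales or price data do not show.

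The size cannot be derived from the document. Under the assumed 0.10 per contact it is about 34-41% against 19-27%. The gap is in the same direction for 0.05 and 0.20, and it narrows if control stores have the manager interview and the second action-plan meeting falls in 2024. The conclusion depends on the contact schedule as published and on there being no prompted harm question elsewhere. The primary outcome is unaffected. The change is worth making because it is cheap and bears on any later statement about harm.

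**What to change.** - Add a short, identical set of items to the Environment Scan in both arms: customer or community complaint, stock write-off, added staff burden, adverse community reaction, other unintended event; yes/no with free text. Ask whether the event occurred in a stated period, whatever its supposed cause, so that control stores can answer on the same terms.
- Use the 2023 round. If it has passed, use a look-back item in the July/August 2024 round, answered before control stores receive feedback or action planning. The control cycle starts with assessment, so this order is available. The look-back from October/November 2022 spans about 20 to 22 months, so recall will be imperfect, but the period is the same in both arms.
- Have a store manager, director or owner answer these items, not only a partner nutritionist.
- Tabulate the answers by randomised arm.
- Take lost sales and price rises from the sales value and price data already collected.
- Keep spontaneous reports as a separate listing and state that it is not compared between arms.

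Cost: about 2 minutes more per respondent on a survey of about 15 minutes, and one extra table. Respondents remain unblinded, so the items equalise the question and its timing, not the perception of events.

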## Ethics and Dissemination

### Research ethics approval

The Benchmarking for Healthy Stores in Aboriginal and Torres Strait Islander communities project has approval from the Miwatj Health Board, Katherine West Health Board, Sunrise Health Board, NT Health Research Governance, the Northern Territory Health and Menzies School of Health Research Human Research Ethics Committee and Aboriginal sub-committee [HREC 2021–4212], the University of Queensland Human Research Ethics Committee [HREC 2022/HE001158], Curtin University Human Research Ethics Committee [HREC 2023–0070] and is registered with Monash University [HREC 2022–30761-73457]. Protocol amendments that may add additional risk to the store participants are communicated to stores prior to seeking approval from the HREC.

### Consent

Written consent is required for participating stores. The consent procedure involves store directors/ owners providing consent for the participation of their store separate to consent to be interviewed and/or participate in the project workshops. Participants provide consent knowing how their data will be managed and their right to have their data withdrawn at any time without prejudice. Informed consent was provided by all participating stores. Additional consent is sought for use of participant data in ancillary studies that may arise.

### Confidentiality

Stores will only be named in public if all participating store businesses specifically request to be named.

### Access to data

Each intervention store and their supporting nutrition practitioner have access to hard-copy reports for their store only, including the policy, practice, price, purchasing and environment scan assessments. User ID and passwords for data collection tools are administered and managed by Monash University and UQ. Research investigators have access to the final datasets. No third party has access to data unless ethics approval and permission from the participating stores is granted.

### Dissemination policy

Following demonstration of effectiveness, we will utilise rapid translation strategies we have used previously. This includes regular stakeholder communication, timely feedback of preliminary results to store directors/owners, use of video to communicate research aims and findings to a broad audience, and workshops to finalise the benchmarking model and determine its embedding int service delivery and policy and its governance. In addition, this study sits within and will harness the translation capabilities and extensive national and international networks of INFORMAS and The Centres of Research Excellence in Food Retail Environments for Health (RE-FRESH) and in Strengthening Systems for Indigenous Health Care Equity [76, 77]. Authorship of publications originating from the Benchmarking for Healthy Stores project is to align with authorship guidelines and national ethical guidelines including the NHMRC Ethical conduct in research with Aboriginal and Torres Strait Islander Peoples and communities: Guidelines for researchers and stakeholders [78]; and the AIATSIS Code of Ethics. for Aboriginal and Torres Strait Islander Research [79]. Authorship must recognise, acknowledge and value the significant contribution to the Benchmarking for Healthy Stores Project of Aboriginal and Torres Strait Islander Peoples knowledges and involvement.

## Discussion

This research will result in a benchmarking model with a proposed governance, workforce and data management structure co-designed with key stakeholders including Aboriginal and Torres Strait Islander community leaders, Aboriginal and Torres Strait Islander store directors, remote food retailers, nutrition practitioners, government policy-makers and academics for its future use.

Its use in the long-term has potential to equip Aboriginal and Torres Strait Islander communities, store directors, retailers, health services, and government policy-makers with knowledge and skills of health-enabling best-practice policy and retail practice. It provides timely information for communities to monitor and strengthen the healthiness of their store and evaluate the impact of change in policy and practice on the healthiness of food and drinks purchased. This research responds to the bold initiatives remote stores are taking to further enable Aboriginal and Torres Strait Islander Peoples make health-enabling evidence-informed policy for their stores and communities.

This novel intervention has potential to support Aboriginal and Torres Strait Islander communities’ impact significantly on reducing the risk of diet-related preventable chronic disease experienced. Diet is one of the leading risk factors for chronic disease worldwide [20]. Changes in store policy and practice for improved population-level diet can benefit the health of all individuals and future generations. Noted though, is that store health-enabling policy and practice can be strengthened with Aboriginal and Torres Strait Islander store directors, however, there are limits to what stores can voluntarily achieve without government intervention to address inequities in food cost in remote communities and regulate the availability and promotion of highly processed unhealthy food and drinks.

## Data Availability

Data collection surveys and consent procedures are available on request. Data are only available to a third party with reasonable written request to the corresponding author and approval received from the project Chief Investigators, Northern Territory Health and Menzies School of Health Research HREC, participating stores and partner organisations.

## Abbreviations

ACCHOs: Aboriginal Community Controlled Organisations
ALPA: Arnhem Land Progress Aboriginal Corporation
AMSANT: Aboriginal Medical Services Alliance Northern Territory
ATNI: Access to Nutrition Initiative
CREATE Critical Appraisal Tool: The Centre of Research Excellence in Aboriginal Chronic Disease Knowledge Translation and Exchange
FIT: Feedback Intervention Theory
INFORMAS: International Network for Food and Obesity/non-communicable diseases Research, Monitoring and Action Support
Katherine West: Katherine West Health Board Aboriginal Corporation
Miwatj: Miwatj Health Aboriginal Corporation
NT Health: Northern Territory Health
NT: Northern Territory
Sunrise: Sunrise Health Service Aboriginal Corporation
